#### Economic evaluation

The aim of the economic evaluation is to compare the costs and health effects of RBC transfusion versus expectant management in women with acute anaemia after PPH. As the clinical study is designed as an equivalence study, the primary economic evaluation is a cost-minimisation analysis. If RBC transfusion is shown to improve the quality of life, the economic analysis will be a cost-effectiveness analysis (time horizon: six weeks postpartum). The analysis will be performed from a hospital perspective. We will calculate direct costs (days in hospital, number of RBC transfusions and costs of complications). Real medical costs will be calculated by multiplying the volumes of health care use with the corresponding cost prices. Unit costs of health care consumption will be estimated according to national guidelines. Data on the volume of care will be available from hospital information systems in the participating hospitals.

Univariate analyses will be used for the analysis of economic outcome data. We will use non-parametric methods to test for differences between treatment groups.

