Acute anaemia postpartum, with fatigue as important symptom, is a clinical problem with wide practice variation in treatment regarding RBC transfusion. There are several arguments against RBC transfusion and the postpartum Hb level seems to influence fatigue for only a short period of time. We therefore aim to show non-inferiority of expectant management versus a transfusion policy regarding physical fatigue, three days after delivery, in postpartum women with an acute anaemia following PPH. The development of a guideline based on clinical parameters, laboratory determinations and HRQoL measures may lead to a more adequate use of RBC transfusions in the postpartum period and possibly reduces costs due to lower frequency of transfusions and hospitalization duration.

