### Study design

The study is a multicentre randomised non-inferiority trial in women with an acute postpartum anaemia. It is an open label study. This trial is embedded in the Dutch Obstetric Consortium, a collaboration of hospitals in the Netherlands [11]. Approximately 40 hospitals, including university hospitals, teaching hospitals and non-teaching hospitals will participate in this trial.

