### Outcome

Primary outcome is physical fatigue on day three postpartum, scored with a dimension of the HRQoL measure MFI. We aim to show non-inferiority of the expectant management arm and therefore this primary assessment day was chosen: if there would be any difference between randomized groups, this difference is expected to be the largest three days postpartum [5]. In total three measures of HRQoL will be scored. Secondary outcomes will be the remaining HRQoL measures and the number of RBC transfusions. In addition an anaemia related symptoms list will be filled in before randomisation and at six weeks postpartum.

Medical process parameters to be evaluated include the increase of Hb level after RBC transfusion and acute transfusion complications. Moreover, we will compare the length of hospital stay and serious physical complications during the first six weeks postpartum (infections, thromboembolic events, hemodynamic events, cardiac events, neurologic events, secondary HPP, obstetric interventions, 'rescue' RBC transfusion). A costs benefit analysis will also be performed (see 'Economic Evaluation').

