### Statistics

#### Sample size

The HRQoL assessments were tested in postpartum women in a pilot study [5]. For the comparison between RBC transfusion and an expectant management a sample size of 400 patients is planned (200 patients in the RBC transfusion group and 200 patients in the expectant management group).  Power calculations showed that with these numbers a difference of 1.3 points or greater in favour of the RBC arm regarding the physical fatigue subscale on day three, the primary outcome, can be excluded with a power of 80% at one-sided alpha of 0.025 assuming that there is no difference on this day [5]. In view of the scale of physical fatigue (ranging from 4 to 20) we think that such a difference is not clinically relevant. Since missing data are not expected to exceed 20%, a total of 500 patients will be included.

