#### Data analysis

Data will be analysed according to the intention to treat principle. The primary outcome, the MFI physical fatigue score at three days postpartum, will be compared between groups using Repeated Measurement ANOVA. This analysis allows for occasional missing values and will be done using an unstructured covariance matrix, while taking account of baseline value (at t = 0) and mode of delivery as covariates. If the two-sided 95% confidence interval for the adjusted difference of means at day three excludes a difference of 1.3 points or greater in favour of the RBC arm, non-inferiority of the expectant policy is considered to be shown [17]. A per-protocol analysis, including only patients without severe protocol violations, will also be performed.

The mean profiles along time of other MFI subscales, SF-36 and EQ-5 D will be compared similarly to the primary outcome measure. The other secondary outcome measures will be assessed by calculating rates in groups, risk differences and 95% confidence interval.

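### The economic evaluation treats a non-inferiority trial as an equivalence study, so an inconclusive result would still be analysed by cost-minimisation, as if effects were equal

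*Protocol article*

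**What the plan says.** The Economic evaluation section gives both the default method and the reason for it: "As the clinical study is designed as an equivalence study, the primary economic evaluation is a cost-minimisation analysis". It states one exception: "If RBC transfusion is shown to improve the quality of life, the economic analysis will be a cost-effectiveness analysis", with a horizon of six weeks postpartum. It states no other condition, and none that refers to the result of the non-inferiority test.

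Elsewhere the design is different:

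- Study design: "The study is a multicentre randomised non-inferiority trial in women with an acute postpartum anaemia".
- Background: "We therefore aim to show non-inferiority of expectant management versus a transfusion policy regarding physical fatigue, three days after delivery".
- Sample size: "Power calculations showed that with these numbers a difference of 1.3 points or greater in favour of the RBC arm" can be excluded "with a power of 80% at one-sided alpha of 0.025 assuming that there is no difference on this day".
- Data analysis: the decision uses one bound of the two-sided 95% confidence interval. If the interval "excludes a difference of 1.3 points or greater in favour of the RBC arm, non-inferiority of the expectant policy is considered to be shown".

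The Abstract's discussion paragraph adds that equivalence of the two policies is assumed.

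**The concern.** Cost-minimisation compares costs alone, so it is justified only when effects can be taken as equal. The protocol takes that justification from the design label, and the label is wrong for this trial. The word matters because it is the stated reason for choosing the method.

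A non-inferiority trial can end in three ways that matter here: non-inferiority is shown, a transfusion benefit is shown, or neither is shown. The economic rule deals explicitly only with the second and leaves everything else under cost-minimisation. In the third case the interval still contains a disadvantage of 1.3 points or more for expectant management, which the trial set out to exclude, yet the economic analysis would proceed as if there were none.

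The likely direction is also not neutral. The Background describes transfusion as costly and as lengthening hospital stay, and the evaluation counts hospital days, transfusions and complications. A comparison of costs alone may therefore lean towards expectant management in a trial that missed its own primary criterion. The Background ties the results to a guideline and to cost savings, so the economic conclusion would carry weight.

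**Working it through.** **Inputs from the protocol (Sample size, Data analysis):** margin 1.3 points on MFI physical fatigue at day 3; one-sided alpha 0.025; power 80%; assumed true difference 0; 200 evaluable patients per arm; up to 20% missing data.

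**The plan's own figure.** 400 / (1 − 0.20) = 500, as stated.

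**Implied SD (not stated in the protocol).** From the usual formula for two means:

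- SE = 1.3 / (1.960 + 0.842) = 0.464
- SD = SE / √(2/200) = 0.464 / 0.1 = 4.64

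With SD 4.64 the formula returns 200 per arm. This shows consistency only, because the SD was solved from that number.

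**Cut-offs.** Let d be the true difference in favour of transfusion.

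- Non-inferiority is shown if the observed difference is below 1.3 − 1.96 × 0.464 = 0.391.
- A transfusion benefit is shown if it is above 1.96 × 0.464 = 0.909.
- Between 0.391 and 0.909 neither is shown. The gap exists because the 95% interval is 2 × 1.96 × 0.464 = 1.82 wide, more than the margin, so one interval can contain both 0 and 1.3.

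**Probability that neither is shown** (normal approximation): Φ((0.909 − d)/0.464) − Φ((0.391 − d)/0.464).

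- d = 0: 0.975 − 0.800 = 0.175
- d = 0.65: 0.712 − 0.288 = 0.424

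**Range over assumed SDs**, with 200 per arm:

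| SD | SE | d = 0 | d = 0.65 |
|---|---|---|---|
| 4.0 | 0.400 | 7.4% | 26.2% |
| 4.64 | 0.464 | 17.5% | 42.4% |
| 5.0 | 0.500 | 23.6% | 49.1% |

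At d = 0.65 and SD 4.64, the probability of staying with cost-minimisation is 1 − 0.288 = 0.712. Of those results, 0.424 / 0.712, about 60%, would lack shown non-inferiority.

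**Is it an equivalence design in effect?** The protocol sets no margin on the other side. If ±1.3 is assumed, the probability of showing two-sided equivalence at d = 0 is 2 × 0.80 − 1 = 0.60. The sample size gives 80% power for non-inferiority, not for equivalence.

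**The case against.** Several points on the other side stand.

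- **The probabilities are illustrative.** The SD is inferred, and adjustment for baseline and mode of delivery could change the SE. The written trigger is improved quality of life, not day-3 physical fatigue. If a benefit on SF-36, EQ-5D or another MFI scale also counts, the switch would occur more often than computed. A reader might take 17.5% or 42% as the chance that cost-minimisation is wrongly run; the documents do not support that reading.
- **The tolerated loss.** A reader might infer that cost-minimisation is wrong even when non-inferiority is shown, because a loss of up to 1.3 points is ignored. The Sample size section says the sponsor regards such a difference as not clinically relevant. Given that judgement, costing alone after a successful test is consistent.
- **Health losses left out.** It would go too far to say that expectant management wins whatever health is lost. Complications and all transfusions are costed, so poor outcomes in that arm add to its cost. The protocol gives no unit costs, so the direction is plausible but not shown. The clinical results are to be analysed whichever economic method is used.
- **A third type of analysis.** The Abstract and the Outcome section speak of a costs benefit analysis. The Outcome section refers the reader to Economic evaluation, so this is loose naming and not a competing plan.

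It can also be said that an article leaves detail to a fuller document. That does not answer the point: the article itself states the wrong design as its reason and fixes both the default and its only exception.

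**Conclusion.** The point holds as a contradiction in the protocol and a gap in a stated rule. The Economic evaluation section rests cost-minimisation on an equivalence design that the trial does not have, and followed as written the rule analyses an inconclusive trial as if effects were equal. This outcome is not remote: about one in six under the planning assumption of no difference, and about four in ten at half the margin. Those figures rest on the implied SD, a normal approximation and day-3 fatigue as a stand-in for quality of life. The contradiction and the gap do not depend on them.

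The consequence is confined to the economic conclusion. The primary endpoint, the sample size and the non-inferiority rule are untouched. Nor does the defect require cost-effectiveness to be the primary economic analysis in every case; only results without shown non-inferiority need a different rule.

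**What to change.** In the Economic evaluation section:

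1. Replace the equivalence label with non-inferiority.
2. Make cost-minimisation the primary economic analysis only if non-inferiority is shown under the Data analysis rule.
3. In all other cases, including an inconclusive result, run the six-week cost-effectiveness analysis already foreseen, and report the cost difference and the effect difference together with their uncertainty. The existing switch on a shown transfusion benefit can stay.

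As an editorial matter, use one name for the evaluation in the Abstract, the Outcome section and Economic evaluation.

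The cost is a few sentences and modest extra analysis. No new data are needed: the Follow-up section already has EQ-5D completed at all five time points.

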## Methods/design

### Aims

The aim of this study is to solve the dilemma for the obstetrician regarding the optimal treatment of women with acute anaemia postpartum. For that reason we determine whether women with acute anaemia postpartum benefit from RBC transfusion.

Our hypothesis is that there is no important difference with regard to physical fatigue, as well as other HRQoL scores and physical complications between RBC transfusion and expectant management as treatment for women with acute postpartum anaemia in the absence of (severe) physical complaints.

If this hypothesis is true, an expectant management is to be preferred to minimise transfusion related reactions and costs.

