### Intervention and control

RBC transfusion will be compared with expectant management.

In patients allocated to RBC transfusion, at least one unit of packed cells will be given. The desired Hb level after transfusion is 5.5 mmol/L (8.9 g/dL). The units of blood will be matched, pre-treated and tested according to the Dutch guidelines for RBC transfusion. Before and 15-90 minutes after transfusion maternal body temperature, blood pressure and heart rate will be checked and a blood sample is taken to determine Hb, haematocrit, platelet and white blood count.

In the group allocated to expectant management, i.e. no RBC transfusion, it is allowed to give a patient 'rescue' RBC transfusion if this is clinically indicated. The indications to give 'rescue' RBC transfusion are secondary PPH, resulting in hemodynamic instability or an Hb value < 3.0 mmol/L (4.8 g/dL), serious physical complaints or other serious general complications. Possible serious physical complaints are: dyspnoea, syncope, orthostatic complaints, tachycardia (> 100 bpm), myocardial ischemia or transient ischemic attacks (TIA).

Additional use of medication to treat anaemia, like oral and parenteral iron medication and other types of medication, is allowed in both groups and may be prescribed according to local protocol. Type and duration of the use of this medication will be recorded.

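### The listed direct costs leave out anaemia medication, so the cost comparison would be biased if its use differs between arms

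*Protocol article*

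**What the plan says.** The Economic evaluation section states that "the primary economic evaluation is a cost-minimisation analysis" and that "The analysis will be performed from a hospital perspective". It then defines what is counted: "We will calculate direct costs (days in hospital, number of RBC transfusions and costs of complications". The sentences that follow describe the method: care volumes are multiplied by prices, unit costs come from national guidelines, and volumes come from the hospitals' information systems. None of them adds a cost item.

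The Intervention and control section allows further treatment of anaemia: "Additional use of medication to treat anaemia, like oral and parenteral iron medication and other types of medication, is allowed in both groups". Prescribing follows local protocol. The same section adds: "Type and duration of the use of this medication will be recorded".

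On blinding, the Study design section says: "It is an open label study". On the use of the result, the Aims section says that if the hypothesis holds, "an expectant management is to be preferred to minimise transfusion related reactions and costs". The Discussion part of the abstract says the same.

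**The concern.** In a cost-minimisation analysis the cost difference is the whole result, so every resource that can differ by arm within the chosen perspective should be counted. The list here counts transfusion, which the design itself makes differ between arms. It does not count iron and other anaemia drugs, which clinicians who know the allocation may prescribe differently.

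Cost is one of the two reasons given for preferring expectant management, the other being fewer transfusion reactions. If women who are not transfused are given more parenteral iron in hospital, that spending disappears from the comparison and the saving looks larger than it is. The trial already records part of what is needed to check this, but the economic section does not use it.

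**Working it through.** The document states no cost result, unit price or rate of medication use, so there is no figure of the plan's own to reproduce. The check has three steps.

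**1. Is medication in the cost list?** The list has three items: hospital days, RBC transfusions and complications. It carries no wording that marks the items as examples. The general sentence on volumes and prices says how items are priced, not which ones. Medication is recorded under Intervention and control, but nothing links that record to the economic analysis. Followed literally, the plan does not price it.

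**2. What does the omission do?** Let *L* be the mean cost per woman of the three listed items and *m* the mean cost of anaemia medication within the hospital perspective, with subscripts R (RBC) and E (expectant).

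- Saving with medication counted: (L_R + m_R) − (L_E + m_E)
- Saving as planned: L_R − L_E
- Bias (planned minus full): m_E − m_R

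For one type of course at unit cost *c*, given to proportions p_E and p_R, the bias is (p_E − p_R) × c. A positive value means the saving is overstated.

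The inputs below are assumptions chosen only to show how the formula behaves: a cost of 10 to 300 currency units per course, and several differences in use.

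| p_E − p_R | Calculation | Bias per woman |
|---|---|---|
| −0.10 | −0.10 × 10; −0.10 × 300 | −1 to −30 (saving understated) |
| 0 | 0 × c | 0 |
| +0.10 | 0.10 × 10; 0.10 × 300 | 1 to 30 |
| +0.30 | 0.30 × 10; 0.30 × 300 | 3 to 90 |
| +0.50 | 0.50 × 10; 0.50 × 300 | 5 to 150 |

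**3. Could use differ by arm?** Women enter with Hb between 3.0 and 5.0 mmol/L. The RBC arm is transfused towards 5.5 mmol/L, which is 5.5 − 5.0 = 0.5 to 5.5 − 3.0 = 2.5 mmol/L above entry. The expectant arm has no transfusion except as rescue. Where prescribing responds to current Hb or to known allocation, more medication in the expectant arm is the natural expectation. The document does not describe the local protocols, so this remains an assumption.

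**The case against.** The strongest reply is that the list need not be exhaustive. The section does not say that only these items count, the general costing sentence could be read to cover medication, and a journal article condenses a fuller protocol in which the items may be spelled out. This has some force, and a reader should not infer that medication was deliberately excluded. But the article does state its cost components, and the sentence after them adds none. At the least the two sections need to be reconciled.

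A second reply concerns the route to imbalance. Medication is allowed in both arms and follows local protocol, and randomisation is stratified by hospital, so differences between hospitals' protocols are balanced. Transfused women may also still qualify for iron, since the target Hb is only 0.5 mmol/L above the upper entry limit. This stands as a reason not to assert a direction. It does not remove the concern, because stratification cannot balance prescribing that responds to Hb or allocation after randomisation.

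Third, oral iron taken at home may fall outside a hospital perspective. That is right, and it limits what must be added.

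Finally, the economic evaluation is secondary. The non-inferiority conclusion on physical fatigue is untouched, and avoiding transfusion reactions remains a separate ground for expectant management. That is also right, and it limits the consequence to the cost claim.

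**Conclusion.** The point holds as a gap in the costing: the stated direct costs omit anaemia medication that is permitted, recorded and, where given in hospital, inside the stated perspective. The resulting bias equals the between-arm difference in use times the unit cost.

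A reader might go further and infer that the saving from expectant management is overstated, or that iron is the main substitute for transfusion in that arm. The document supports neither. It gives no use by arm and no prices, so both direction and size are open, and it describes the medication as additional treatment available to both arms. An overstated saving requires more use in the expectant arm, which is plausible but unproven. Any range that starts from a positive excess has assumed the direction. The figures in the table are illustrations only. They are not compared with the cost of a transfusion or a hospital day, for which no price is given, so they do not show that the bias would be material.

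**What to change.** In the Economic evaluation section, add anaemia medication that falls within the hospital perspective to the direct costs of both arms. This should include at least parenteral iron given in hospital, together with the cost of administering it. Take volumes from the recorded medication data or the hospital information systems, whichever gives a quantity that can be priced, and use the same national unit costs as for the other items. Report anaemia medication use by arm beside the cost result, so that readers can see whether it differed. Oral iron taken at home can go into a sensitivity analysis.

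The cost is a few unit prices and a little more analysis. Treatment, randomisation and the primary outcome are unaffected. The saving may become slightly less favourable to expectant management; if use proves equal, the result is unchanged and better supported.

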### Procedures, recruitment, randomisation and collection of baseline data

Eligible patients receive participant information. After written consent, participants are randomised by means of a web-based application [12]. Randomisation will be blocked in a 1:1 ratio for RBC transfusion or expectant management. Stratification will be applied for mode of delivery and participating hospital.

All data will be collected, coded and processed with adequate precautions to ensure patient confidentiality.

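### The economic comparison is planned as univariate although randomisation is stratified by mode of delivery; to the extent that mode predicts cost or days in hospital, the test is conservative and loses some power

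*Protocol article*

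**What the plan says.** All places are in the protocol article.

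- **Procedures, recruitment, randomisation and collection of baseline data:** "Randomisation will be blocked in a 1:1 ratio for RBC transfusion or expectant management", and "Stratification will be applied for mode of delivery and participating hospital".
- **Data analysis:** the primary fatigue model is fitted "while taking account of baseline value (at t = 0) and mode of delivery as covariates". The other MFI subscales, SF-36 and EQ-5D are to be compared in a similar way.
- **Economic evaluation:** "Univariate analyses will be used for the analysis of economic outcome data", followed by "We will use non-parametric methods to test for differences between treatment groups". No covariate or stratum is named. Days in hospital are one of three listed cost components, beside RBC transfusions and complications.

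Mode of delivery is thus used in the design and in the quality-of-life models, but not in the stated method for costs.

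**The concern.** When arms are balanced within a factor that predicts the outcome, the arm difference varies less from trial to trial than a simple two-group comparison supposes. The two-group test keeps the between-factor variation in its noise term. It then rejects less often than its nominal level under no difference, and less often than it could under a real one. This holds for means and for ranks, so it does not depend on which statistic is chosen.

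Mode of delivery is a plausible predictor here. The investigators chose it as a stratifier, and the Background reports more blood loss at caesarean section. The Aims give lower cost as one of two reasons to prefer expectant management, and cost-minimisation is the primary economic evaluation. An analysis that ignores a factor already known for every randomised woman gives away precision for nothing.

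**Working it through.** **Inputs from the article.** 1:1 blocked randomisation, stratified by mode of delivery and hospital; about 40 hospitals; 200 evaluable women per arm. The sample-size inflation reproduces: 400 / (1 − 0.20) = 500, or 250 per arm. The article gives no standard deviation, effect size or power for costs, so there is no economic figure to reproduce.

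**Assumed input.** R², the share of outcome variance explained by mode of delivery. The article does not give it, so a range is shown.

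**Step 1: closed form.** With balance on mode, true SE = unadjusted SE × √(1 − R²). For a nominal two-sided 5% test:

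- true alpha = 2[1 − Φ(1.96 / √(1 − R²))]
- unadjusted power, when adjusted power is 80%, = Φ(1.96 + 0.8416 − 1.96 / √(1 − R²))

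Example, R² = 0.20: 1.96 / 0.8944 = 2.191; alpha = 2[1 − Φ(2.191)] = 2.8%; power = Φ(2.802 − 2.191) = Φ(0.610) = 72.9%.

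| R² | Unadjusted SE / true SE | True alpha | Unadjusted power (adjusted = 80%) |
|---|---|---|---|
| 0 | 1.000 | 5.0% | 80.0% |
| 0.02 | 1.010 | 4.8% | 79.4% |
| 0.05 | 1.026 | 4.4% | 78.5% |
| 0.10 | 1.054 | 3.9% | 76.9% |
| 0.20 | 1.118 | 2.8% | 72.9% |
| 0.30 | 1.195 | 1.9% | 67.7% |

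**Step 2: simulation with the trial's structure.** 500 women, 40 hospitals, permuted blocks of 4 (block size assumed) within hospital and mode, log-normal cost, caesarean share 20% or 40%, 2000 runs per setting.

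| R² (approx.) | Mann-Whitney power | Mode-stratified rank test power |
|---|---|---|
| 0 | 80–82% | 80–82% |
| 0.06–0.07 | 78–79% | 80–81% |
| 0.20–0.23 | 71–75% | 82% |
| 0.37 | 56–66% | 80% |

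At R² 0.20–0.23 the Mann-Whitney false-positive rate was 2.0–3.4%, and the unadjusted SE for means was 9–12% too large. That is slightly less than the closed form gives, because incomplete blocks in small strata leave the balance imperfect.

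**Step 3: what R² could mean for days in hospital.** All figures here are assumptions: mean stay 2.5 days after vaginal delivery, coefficient of variation 0.5, 250 per arm, arm difference 0.35 day, 30% caesarean, stay 2 days longer after caesarean.

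- Within-mode variance: 0.7 × 1.25² + 0.3 × 2.25² = 2.61
- Between-mode variance: 0.3 × 0.7 × 2² = 0.84
- R² = 0.84 / 3.45 = 0.24
- Unadjusted SE = √(3.45 × 2/250) = 0.166; true SE = √(2.61 × 2/250) = 0.145
- Unadjusted power = Φ((0.35 − 1.96 × 0.166) / 0.145) ≈ 57%
- Adjusted power = Φ(0.35 / 0.145 − 1.96) ≈ 68%
- True alpha ≈ 2.4%

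With caesarean shares of 20–40%, a 1-day gap gives R² 0.08–0.10 and a gain of 2–3 points. A 3-day gap gives R² 0.34–0.36 and a gain of 18–19 points.

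**Step 4: total cost.** Transfusion use differs by design, which adds a cost difference whatever the stay. Assume 1.8 units per woman in the RBC arm, 13% of the expectant arm rescued with 2 units, and one unit costing as much as 0.25 hospital day. The added difference is 0.25 × (1.8 − 0.26) = 0.385 day-equivalents. With the 2-day gap of step 3:

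- Stay also 0.35 day longer in the RBC arm: power is about 99–100% with or without adjustment, for ranks and for means.
- No difference in stay: about 84% (unstratified) against 88–89% (stratified) for ranks, and about 67% against 77% for means.
- One unit costing 0.5 day: practically 100% for all of them.

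**The case against.** **The wording may not exclude a stratum.** *Univariate* can mean one outcome at a time, and a stratified rank test is also non-parametric. A condensed article may leave such detail to a fuller plan. This stands as a caution. Set beside a Data analysis section that does name its covariates, arm against arm without covariates remains the more natural reading, and the wording is worth settling either way.

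**The size rests on assumptions.** This stands. The article gives no cost or stay by mode of delivery. At R² of 0.05 or below the loss is negligible, and at zero there is none.

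**Stronger readings that a reader might infer, and that the documents do not support:**

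- *That hospital stay is the main cost driver.* It is listed first of three components; nothing ranks them by size.
- *That the cost confidence interval will be too wide.* The section plans tests and describes no interval for costs. The point about width applies only if an unadjusted interval is reported.
- *That a real saving in total cost will be missed.* Step 4 shows that power for total cost may be high already. A material gain there needs cheap transfusion and little or no difference in stay.
- *That length of stay is assigned an unadjusted test under Data analysis.* The sentence for other secondary outcomes, "The other secondary outcome measures will be assessed by calculating rates in groups, risk differences and 95% confidence interval", describes methods for binary outcomes and fixes no test for stay.

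**Hospital is also a stratifier.** The same logic applies to it in principle, and it is not quantified here. The quality-of-life models name mode and not hospital, so adjusting for mode at least puts the economic analysis on the same footing.

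**Conclusion.** The point holds in a conditional form. The stated economic comparison ignores a factor that the trial randomises by and adjusts for elsewhere. If mode of delivery explains about 10–20% of the variance in cost or days in hospital, the unstratified test gives up about 3–7 points from 80% power and runs at a true alpha of about 3.9–2.8%. At 5% or less the loss is 1–2 points and can be ignored. These figures rest on assumed R² values and on near balance within mode.

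The error is on the conservative side. With arms balanced by mode, the estimated mean difference is essentially unchanged, so there is no bias and no added false-positive risk. The outcome is secondary, and the non-inferiority conclusion on fatigue is not affected. The practical gain lies mainly in days in hospital, or in total cost if transfusion cost is small. This is a free improvement of minor priority, not a defect that threatens the trial's findings.

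**What to change.** In Economic evaluation, replace the sentence "Univariate analyses will be used for the analysis of economic outcome data" with: *Costs and days in hospital will be compared between arms adjusted for mode of delivery.* Then name the method: a linear model for the mean cost difference with mode of delivery as covariate and a robust or bootstrap interval or, if a rank test is kept, a van Elteren test stratified by mode of delivery.

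The cost is a sentence or two of wording and a slightly longer program. No new data are needed, because mode of delivery is known for every woman at randomisation. Fixing it in advance also avoids a later choice between adjusted and unadjusted results once the data are seen.
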